## Figures and Tables

**Figure 1 jcm-14-07327-f001:**
[figure not shown]
Workflow for model building and evaluation.

**Figure 2 jcm-14-07327-f002:**
[figure not shown]
Overview of 5 × 2 nested cross-validation.

**Table 2 jcm-14-07327-t002:** Search spaces for hyperparameter tuning.

Model		Hyperparameter	Values
LR		C (L2 regularisation strength)	[0.01, 0.1, 1, 10, 100]
		max_iter	[100, 200, 500]
XGBoost		n_estimators	[50, 100, 200]
		learning_rate	[0.01, 0.1, 0.2]
		max_depth	[3, 5, 7, 9]
MLP	Pretraining	units (hidden layer sizes)	[32, 64, 128, 256, 512]
		hidden_layers	[1, 2, 3, 4]
		activation	[‘relu’, ‘tanh’]
		learning_rate	[0.0001, 0.001, 0.01]
		kernel_regularizer = l2()	[0.000001, 0.00001, 0.0001, 0.001, 0.01, 0.1]
		dropout (dropout rate)	[0.1, 0.2, 0.3, 0.4, 0.5]
	Fine-tuning	units (hidden layer sizes)	[32, 64, 128, 256, 512]
		hidden_layers	[1, 2, 3, 4]
		activation	[‘relu’, ‘tanh’]
		learning_rate	[0.000001, 0.00001, 0.0001]
		kernel_regularizer = l2()	[0.000001, 0.00001, 0.0001, 0.001, 0.01, 0.1]
		dropout	[0.1, 0.2, 0.3, 0.4, 0.5]
		Freezing layers	Custom implementation

**Table 3 jcm-14-07327-t003:** Updating analyses; primary.

Questions	Hypotheses	Outcome Measures	Sampling Plan (*N*, Power Analyses)	Analysis Plan	Interpretation Given to Different Outcomes
Primary: Does the acute context of AFAIS, and the importance of the index event, call for a CPR bespoke to early secondary prevention? In other words, are the main effects of the constituent features of CHA_2_DS_2_-VASc different post-stroke? Besides main effects, are there synergistic or other non-linear interaction effects between stroke history and the constituent features of CHA_2_DS_2_-VASc that can further improve prediction of 90-day AFAIS recurrence? Secondary: How do CPRs trained to capture 90-day AFAIS recurrence perform with regard to secondary outcomes (7-day recurrence, 7- and 90-day HT, 90-day decline in functional status, and 90-day all-cause mortality)? Exploratory: How do CPRs trained to capture 90-day AFAIS recurrence perform with regard to recurrence among non-AF AIS patients?	Primary: LR and XGBoost can capture the main effects of the constituent features of CHA_2_DS_2_-VASc in the context of secondary prevention. XGBoost is also equipped to capture complex functional relationships between the features. The outputs of these models can be employed to construct CPRs that outperform CHA_2_DS_2_-VASc for predicting 90-day recurrence in AFAIS patients. Specifically, fair (AUC < 0.8) to good (< 0.9) discrimination can be achieved for this high-risk group, alongside improved calibration and clinical utility relative to CHA_2_DS_2_-VASc. Secondary: The resulting CPRs also outperform CHA_2_DS_2_-VASc for predicting secondary outcomes.	LR and XGBoost models: Discrimination assessed using AUC and calibration curves. Calibration assessed using calibration curves, slopes, and Brier scores. Additional metrics: F1 score, accuracy, precision, sensitivity, specificity, Youden index, PPV, NPR, PLR, NLR. Resulting CPRs: Discrimination assessed using AUC and calibration curves. Calibration assessed using calibration curves, slopes, and Brier scores. Clinical utility assessed via DCA relative to default strategies as well as CHA_2_DS_2_-VASc. Test tradeoff analysis will be used to balance ease-of-use with clinical utility.	Primary: LR—680 patients deemed necessary, see Appendix S5.3 in Supplementary Materials file S3. XGBoost—learning curve analysis and KL divergence will afford post hoc insight on suitability of sample size. 75% of AF dataset will be used, comprising 2072 AFAIS patients. Remaining 25% (691 patients) will be withheld as test set. Secondary: Entire AF dataset will be used, comprising 2763 AFAIS patients. Exploratory: Entire non-AF dataset will be used as supplementary test set, comprising 7809 AIS patients.	Models will be instantiated (LR with L2 regularisation and XGBoost with default hyperparameters) on AF dataset, randomly split into training (***T***, 75%) and test sets (***t***, 25%), preserving distribution of outcomes. Nested cross-validation (5 × 2) will be employed for training and hyperparameter tuning. After hyperparameters are optimised, final models will be retrained using the entire training set. The test set ***t*** will then be used for evaluation of final LR and XGBoost models, focusing on discrimination and calibration. Feature importance will be reported via coefficients and odds ratios (ORs) for LR and feature gain for XGBoost. To derive CPRs from these models, SHAP will quantify both main effects and interaction effects of predictor variables. Main effects, represented by mean SHAP values, will be used to rank and assign scores to each predictor, enabling the creation of interpretable and clinically applicable CPRs. Interaction effects, captured through SHAP interaction values, will further refine our CPRs by identifying significant synergistic or redundant relationships between predictors. These interactions will be incorporated into so-called ‘augmented CPRs’ in the form of accompanying rules. Both non-augmented and augmented CPRs will be evaluated on the test set ***t*** in terms of discrimination, calibration, and clinical utility. Clinical utility will be measured using NB via DCA, plotting NB against risk thresholds within the 0.01–0.20 range. The CPRs will be compared on the basis of clinical utility to one another, CHA_2_DS_2_-VASc, and default strategies (‘treat all’ and ‘treat none’). Test tradeoff analysis will evaluate whether any incremental benefit in clinical utility observed with augmented CPRs justifies the added complexity of incorporating accompanying rules. Secondary: CPRs (and not models) will be evaluated on the entire AF dataset for each secondary outcome via discrimination, calibration, and clinical utility. Exploratory: CPRs (and not models) will be evaluated on the entire non-AF cohort to assess generalisability and compare their clinical utility when applied to an unseen yet closely related patient population.	Discrimination will be classified as follows [101]: AUC of 0.81–0.90 = good, 0.71–0.80 = fair, 0.61–0.70 = modest, and 0.51–0.60 = poor. Miscalibration is detrimental to medical decision making and poor calibration has been coined the Achilles heel for CPR applicability [102]. As such, we consider at least as important as discrimination and give precedence to clinical utility, which provides a more comprehensive evaluation by integrating both discrimination and calibration when interpreting the performance of our CPRs. CPRs will be considered clinically useful at a given risk threshold only if their NBs exceed those of both default strategies. Of those deemed useful, we will rank the CPRs (including CHA_2_DS_2_-VASc) based on NB across the 0.01–0.20 risk thresholds. Test tradeoff (∆*N**B*) will be interpreted only insofar as spotlighting those CPRs which would be more conveniently deployable without sacrificing significant clinical utility.

**Table 4 jcm-14-07327-t004:** Updating analyses; secondary.

Questions	Hypotheses	Outcome Measures	Sampling Plan (*N*, Power Analyses)	Analysis Plan	Interpretation Given to Different Outcomes
Primary: Does the acute context of AFAIS, and the importance of the index event, call for a CPR bespoke to early secondary prevention? In other words, are the main effects of the constituent features of CHA_2_DS_2_-VASc different post-stroke? Besides main effects, are there synergistic or other non-linear interaction effects between stroke history and the constituent features of CHA_2_DS_2_-VASc that can further improve prediction of 90-day AFAIS recurrence? Secondary: How do CPRs trained to capture 90-day AFAIS recurrence perform with regard to secondary outcomes (7-day recurrence, 7- and 90-day HT, 90-day decline in functional status, and 90-day all-cause mortality)?	Primary: MLP can capture the main effects of the constituent features of CHA_2_DS_2_-VASc in the context of secondary prevention, as well as complex functional relationships between stroke history and the other features. Its output can be employed to construct CPRs that outperform CHA_2_DS_2_-VASc for predicting 90-day recurrence in AFAIS patients. Specifically, fair (AUC <0.8) to good (<0.9) discrimination can be achieved for this high-risk group, alongside improved calibration and clinical utility relative to CHA_2_DS_2_-VASc. Secondary: The resulting CPRs also outperform CHA_2_DS_2_-VASc for predicting secondary outcomes.	See Table 3.	Learning curve analysis and KL divergence will afford post hoc insight on suitability of sample size. Data augmentation via transfer learning is particularly valuable for DL models like MLP, which are very data-hungry. Entire non-AF dataset will be used in pretraining phase, comprising 7809 AIS patients. 75% of AF dataset (***T***) will be used in fine-tuning phase, comprising 2072 AFAIS patients. Remaining 25% of AF dataset (***t***, 691 patients) will be withheld as test set.	The MLP model will leverage information within the non-AF patient dataset during pretraining. Non-AF AIS patients, who were not included in training the LR and XGBoost models—and therefore in no capacity informed the CPRs constructed thus far—may improve CPR generalisability and clinical utility. We contend our use case is well-suited to transfer learning given that the features of CHA_2_DS_2_-VASc are known to increase risk of AIS in patients without AF, and it has been reported to be equally predictive in the absence of AF [40]. MLP will be instantiated using default hyperparameters and undergo training, hyperparameter tuning, and retraining on the entire non-AF dataset to yield the pretrained model. The pretrained model will be evaluated (AUC, F1 score, precision, sensitivity, specificity) and its last layer(s) removed. These will be replaced by new, naive layers that culminate in an output layer with two neurons. The resulting neural network will be trained on the training set ***T***. Two strategies will be tried: fine-tuning and freezing. In either case, the training phase will again employ nested CV (5 × 2) and the fine-tuned model will be retrained on the AF training set. Training performance will be reported using AUC, F1 score, accuracy, precision, sensitivity, and specificity, used to inform whether the purely fine-tuned or the frozen model will be retained for evaluation on the test set ***t***. To derive CPRs from the MLP model’s output, SHAP will quantify main and interaction effects of predictor variables. Main effects, represented by mean SHAP values, will be used to rank and assign scores to each predictor. Interaction effects, captured through SHAP interaction values, will further refine our CPR by identifying significant synergistic or redundant relationships between predictors. These interactions will be incorporated into an ‘augmented CPR’ in the form of accompanying rules. Both non-augmented and augmented CPRs will be evaluated on the test set ***t*** in terms of discrimination, calibration, and clinical utility. The CPRs will be compared on the basis of clinical utility to one another, LR- and XGBoost-informed CPRs, CHA_2_DS_2_-VASc, and default strategies (‘treat all’ and ‘treat none’). Test tradeoff analysis will be performed. Secondary: CPRs (and not the MLP model) will be evaluated on the test set ***t*** for each secondary outcome via discrimination, calibration, and clinical utility.	See Table 3.

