### 2.4. Predictor Variables

The predictor variable in the validation analyses is CHA_2_DS_2_-VASc score, computed on the basis of its constituent features. It is computed as follows: 1 point for each of CHF, hypertension, DM, vascular disease (MI, CAD, or peripheral artery disease), age 65–74 years, and sex category (female), and 2 points for each of age ≥ 75 years and antecedents of AIS or TIA [24]. All features were measured at baseline, and, with the exception of age, all were binary encoded. As one of the more subjective items considered by CHA_2_DS_2_-VASc, peripheral artery disease was seldom recorded by contributing trials. Hence, MI and CAD will underlie the vascular disease feature.

The predictor variables in the updating analyses are the constituent features of CHA_2_DS_2_-VASc—omitting S_2_, which provides no discriminatory information in a cohort where all patients inherently have the same value (i.e., 2)—and previous stroke. Crucially, since secondary prevention is, by definition, aimed at patients having sustained an AIS, previous stroke is defined herein as any episode of AIS *prior* to the one that prompted recruitment. Besides preserving the familiar 7-feature structure of CHA_2_DS_2_-VASc, incorporating this variable in the updated CPR is very apropos in the modern-day context of effective treatment and demographic ageing which signify that many patients survive one or more strokes.

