##### CPR Development

SHAP will be used to ‘translate’ model insights into CPRs. Mean—and not mean *absolute*—SHAP values will be used in order to preserve information on the directionality of feature importance. The decile rank of each of the eight mean SHAP values from each model will be calculated and a dot plot will be provided to visualise each feature’s mean SHAP value relative to others. (We speak of eight mean SHAP values because we have eight predictor variables corresponding to the features of CHA_2_DS_2_-VASc, namely five comorbid items, sex, and *two* age categories [65–74 years and ≥75 years]). The 25th, 50th, and 75th percentiles of the eight mean SHAP values will be computed. We will subsequently rank the features from most to least important and sort them into three tiers: (1) the lower tier grouping features with mean SHAP values below the 25th percentile, (2) the middle tier grouping features with mean SHAP values between the 25th and 75th percentiles, and (3) the upper tier grouping features with mean SHAP values above the 75th percentile. Features belonging to the lower, middle, and upper tiers will be assigned one, two, and three points, respectively. The purpose of a larger middle tier is to avoid over- or understating the importance of features by promoting stability over frequent changes with minor shifts in model parameters. In the rather unlikely event that one or more features will have negative mean SHAP values and local SHAP value distributions that are consistently left of zero on the beeswarm plots, zero points will be assigned, because their inclusion would degrade 90-day recurrence predictive performance. Ties at quantile cut-points will be resolved conservatively by assigning them to the higher category (e.g., features tied at the 75th percentile will enter the upper tier). The resulting CPRs will be summarised in tabular form and given an acronym in likeness to CHA_2_DS_2_-VASc.

If the dot plot suggests that the distribution of mean SHAP values is very skewed or concentrated, the above-defined tiers will probably inadequately capture features of lower, intermediate, and higher importance. In this eventuality, we will tailor tier boundaries using quantile-based binning. After adapting the tier setup to the observed clusters, we will define lower, middle, and upper tiers whose features will be assigned one, two, and three points, respectively.

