Each of the CPRs will subsequently be augmented by integrating interaction effects. This purports to better accommodate for the fact that a given feature may be more impactful in the presence of one of its counterparts. Mean (and not mean *absolute*) SHAP interaction values will be used in order to distinguish between synergistic and redundant interactions. The decile rank of each of the twenty-eight mean SHAP interaction values from each model will be calculated. A dot plot will be provided to visualise each feature-pair’s mean SHAP interaction value relative to other pairs. (We speak of twenty-eight mean SHAP interaction values because there are eight features, and (*i*, *j*)- and (*j*, *i*)-values capture the same interaction effect, while (*k*, *k*)-values capture main effects and were the object of the above paragraph). Dealing with a large number of feature-pairs, we will use stringent percentiles in selecting interaction effects for inclusion. The 90th percentile of the sample of twenty-eight mean SHAP interaction values will be computed. Feature-pairs with mean SHAP values above this threshold will be selected as the most important synergisms. Feature-pair selection will also incorporate domain knowledge, as some feature-pairs have well-established synergisms that may merit inclusion even if they fall somewhat short of the 90th percentile cutoff. Examples include CHF and age [121], hypertension and age [122], and hypertension and DM [123]. Selected feature-pairs will be integrated into the CPRs as accompanying rules: ‘if both feature *i* and *j* of the pair are present in the patient, add one additional point to the patient’s total score’. To mitigate overfitting, we will cap the number of points that can be added to accommodate synergisms to three. We will further cap the number of interaction pairs retained at a maximum of three. The augmented CPRs will be summarised in tabular form and their acronyms labelled with an asterisk (e.g., CHA_2_DS_2_-VASc*). A worked example of the CPR development process here described can be found in Appendix S6 in Supplementary Materials file S3.

Both non-augmented and augmented CPRs will undergo evaluation. See “CPR Evaluation”.

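### Table 3 asks whether the CHA2DS2-VASc main effects differ after stroke, but no planned comparison could answer no, and the scoring rules return new weights and interactions regardless

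*Protocol article*

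**What the plan says.** The Questions column of Table 3 opens with whether a rule specific to early secondary prevention is called for. It restates this as "are the main effects of the constituent features of CHA_2_DS_2_-VASc different post-stroke" and then asks "are there synergistic or other non-linear interaction effects between stroke history and the constituent features".

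Section 2.4 gives the existing weights: "1 point for each of CHF, hypertension, DM, vascular disease", with age 65–74 and female sex also at 1, and "2 points for each of age ≥ 75 years and antecedents of AIS or TIA". The updated rule has eight features, "namely five comorbid items, sex, and *two* age categories", one of them being a stroke before the index event.

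Under CPR Development, mean SHAP values are cut at the 25th and 75th percentiles: "Features belonging to the lower, middle, and upper tiers will be assigned one, two, and three points, respectively". Features that are consistently negative get zero. If the values are skewed or concentrated, the boundaries are reset, but "we will define lower, middle, and upper tiers whose features will be assigned one, two, and three points, respectively".

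For interactions, "We speak of twenty-eight mean SHAP interaction values because there are eight features". Pairs above the 90th percentile are kept. Domain knowledge may add pairs that fall somewhat short, and at most three pairs are retained.

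Model Building reports LR coefficients and odds ratios with 95% intervals. CPR Evaluation and Table 3 compare the new rules with CHA2DS2-VASc on discrimination, calibration and net benefit.

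**The concern.** Whether effects differ from the existing weights is a question about coefficients. It needs estimates, their uncertainty, and a comparison with the existing weights. The plan has the first two for LR main effects only, and the comparison nowhere. What it does produce is a point table fixed by rank, which says which features come out higher or lower but not whether the spacing departs from CHA2DS2-VASc.

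The interaction question has the same gap. A percentile cut on 28 values picks the largest values whether or not any interaction exists. No uncertainty measure or absolute criterion is stated for these values, although Table 3 speaks of identifying significant relationships.

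At stake is how the results can be read. A table with new points and a few synergy rules looks like evidence that risk factors act differently after stroke, and a reader could not separate a real departure from the output of the scoring rule.

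**Working it through.** **Tier rule.** Inputs: eight distinct mean SHAP values, and cuts at the 25th and 75th percentiles with linear interpolation (numpy's default; the analyses are to be run in Python).
- Lower cut: 0.25 × 7 = 1.75 steps above the smallest value, between the 2nd and 3rd values, so 2 features lie below.
- Upper cut: 0.75 × 7 = 5.25 steps, between the 6th and 7th values, so 2 features lie above.
- Points: {1,1,2,2,2,2,3,3}, whatever the data.

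The existing weights on the same features, with previous stroke at 2, are {1,1,1,1,1,1,2,2}. Six items share one weight there, while the rule lets at most four share one. The existing pattern, or any multiple of it, therefore cannot be returned. In simulations with the existing weights true (0.25 log-odds per point, assumed prevalences, event rates about 7% and 21%), the rule returned them in 0 of 400 data sets at each rate.

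**Exceptions.** The zero-point rule only lowers features and cannot make six share a non-zero weight. The fallback leaves tier sizes open. It could give six items 1 point, age ≥ 75 two and previous stroke three, but its 3-point tier excludes the existing set.

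**Interaction rule.** The plan's 28 reproduces: 8 × 7 / 2 = 28, of which 7 contain previous stroke and 21 do not. The 90th percentile lies 0.9 × 27 = 24.3 steps above the smallest value, between the 25th and 26th values, so 28 − 25 = 3 pairs are kept. If the ranking were pure chance, the probability that at least one of the three involves previous stroke is 1 − C(21,3)/C(28,3) = 1 − 1330/3276 = 0.594. This applies to models that give distinct values. The planned LR lists no product terms, so on the log-odds scale its interaction values would all be zero.

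**Can a test answer no?** Take T with n = 2072 and three ordinary logistic models:
- M0: intercept, slope × CHA2DS2-VASc, prior AIS (2 slopes; the index-stroke points are constant in this cohort).
- M1: eight free coefficients.
- M2: M1 plus 7 prior-AIS products (15 slopes).

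Degrees of freedom: 8 − 2 = 6 for M1 against M0, and 15 − 8 = 7 for M2 against M1. With the existing weights true (assumed prevalences, 0.25 log-odds per point, 1,000 runs each), rejection at recurrence rates of 5, 10 and 24% was 5.0, 4.1 and 4.9% for the first test and 6.7, 6.0 and 4.9% for the second. Repeated simulation gave about 4–6% and 5–8%, with occasional non-convergence of a fit.

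**Information available.** Over the plan's recurrence range, T has 0.05 × 2072 ≈ 104 to 0.25 × 2072 = 518 events. For M2 at the lower end that is 104 / 15 ≈ 7 events per coefficient.

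**The case against.** The strongest reply is that this is a prediction study judged on held-out performance. Table 3's hypotheses say that the new rules will outperform CHA2DS2-VASc, and that can fail: CHA2DS2-VASc is in the net-benefit ranking, and augmented rules are compared with plain ones. This stands. A reader might infer that the whole primary question cannot be answered no. The documents do not support that for the wider question of whether a bespoke rule is needed. But better performance and different effects are separate matters, and Table 3 asks about both.

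A reader might also infer that the stroke-history interactions are not estimated at all. They are: all seven are among the 28 SHAP values. What is missing is a test, a stated uncertainty, or any separate treatment of them.

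It is also fair that no passage says different points prove different effects, and that LR odds ratios with intervals will be visible. Those intervals, however, come from a ridge-penalised, class-weighted fit (sections 2.8 and 2.12.6) and are set against nothing.

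Finally, rejecting M0 would not show a change caused by stroke. The cohort has no stroke-free comparator. Section 2.11 describes a development study with a 1-year thromboembolism outcome in patients on neither VKAs nor heparin; here the outcome is 90-day AIS and some patients receive VKAs. This stands and limits the wording of any positive result.

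**Conclusion.** The point holds for the main-effects sub-question and for whether stroke-history interactions exist: neither has a planned comparison or criterion that could return no. Under the default tier rule, new weights are certain given distinct values and the usual interpolated percentiles. Other percentile definitions can move the tier counts to 1, 4 and 3 or keep two pairs instead of three, but still let no more than four features share a weight.

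The loss is in interpretation, not discrimination. With the existing weights true, the 15 correctly ordered default-rule scores had AUCs of 0.5815–0.5832 against 0.5836, a difference of 0.0004 to 0.0021 under assumed inputs. The null rejection rates also rest on assumed prevalences and effect size. No power figure is offered, because it would depend on departures that the documents do not specify.

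**What to change.** Add to the Analysis Plan column of Table 3, on T, using ordinary unweighted and unpenalised logistic regression:
1. M1 against M0 (6 df), with each item's departure from its existing weight and a confidence interval, for the main-effects question.
2. M2 against M1 (7 df) for the stroke-history question, with a penalised-likelihood fit if sparse cells prevent convergence.

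Add to the Interpretation column:
- Different tier points or selected pairs are not in themselves evidence of different effects.
- A positive first test means that the existing weights do not fit 90-day recurrence in this AFAIS cohort. It does not show a change due to stroke.
- Non-rejection is inconclusive where the intervals are wide.

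The tier rules, the SHAP analyses and the net-benefit ranking can stay as they are. The cost is three regressions and a few lines of text. The downside is modest power near 5% recurrence, with about 104 events in T, which should be stated beside the tests.

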##### CPR Evaluation

We will evaluate the CPRs on the test set ***t*** using discrimination, calibration, and clinical utility. The same methodology previously applied to CHA_2_DS_2_-VASc will be used to assess the discrimination and calibration of the newly developed CPRs. See Section 2.12.4. Clinical utility will be measured using net benefit (NB) via decision curve analysis (DCA). Although a CPR with better discrimination and calibration should, in theory, better guide clinical management, discrimination and calibration cannot determine whether a CPR aids decision making or which of several CPRs leads to better decisions. This is especially true when some CPRs have better discrimination and others better calibration. The shortcomings of conventional measures of performance are due to the fact that they do not incorporate information on consequences. DCA incorporates consequences by considering the tradeoffs between the benefits of true positives and the harms of false positives across a range of risk thresholds that reflect a spectrum of possible patient and clinician preferences [100]. It achieves this by calculating the NB for each risk threshold (*p**t*), which is defined as the number of true positives corrected for the number of false positives weighted by the odds of the risk threshold, all divided by the sample size (*N*) [124]. This is equivalent to the proportion of true positives in the absence of false positives (i.e., perfect specificity). To effectively use CPRs in clinical management, it is necessary to specify the risk thresholds at which intervention would be warranted. For early secondary prevention of AFAIS, oral anticoagulation is the treatment, and risk thresholds within 0.01—0.20 are reasonable. We will thus calculate the true positives and false positives for each CPR across the 0.01–0.20 risk threshold range and compute NB using the following formula:$$NB=\frac{\;\mathrm{True}\;\mathrm{positives}\;}{N}-\frac{\;\mathrm{False}\;\mathrm{positives}\;}{N}\left(\frac{p_{t}}{1-p_{t}}\right).\;$$

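### Table 3 scores the LR- and XGBoost-derived CPRs for secondary outcomes mostly on their own training patients, while Table 4 and the CPR Evaluation section use the held-out set

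*Protocol article*

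**What the plan says.** Table 3 (Updating analyses; primary) covers the CPRs built from LR and XGBoost. Its sampling plan assigns the training data: "75% of AF dataset will be used, comprising 2072 AFAIS patients". It then sets the rest aside: "Remaining 25% (691 patients) will be withheld as test set". For secondary outcomes the same cell says "Secondary: Entire AF dataset will be used, comprising 2763 AFAIS patients", and the analysis plan repeats it: "Secondary: CPRs (and not models) will be evaluated on the entire AF dataset for each secondary outcome via discrimination, calibration, and clinical utility".

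Table 4 (Updating analyses; secondary) covers the MLP-derived CPRs. The AF training set T "will be used in fine-tuning phase, comprising 2072 AFAIS patients". For the same secondary outcomes the rule differs: "Secondary: CPRs (and not the MLP model) will be evaluated on the test set" t.

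The CPR Evaluation section opens with "We will evaluate the CPRs on the test set" t and makes no exception for secondary outcomes. The Test Set section keeps t separate from model building. No reason is given for the difference between the tables, and no optimism correction is planned.

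**The concern.** A score tested on the patients who shaped it looks better than it will in new patients. Table 3 states the secondary hypothesis that the new CPRs do better than CHA2DS2-VASc on the secondary outcomes, with no margin, so even a small one-sided gain counts in its favour. CHA2DS2-VASc took nothing from these data and carries no such gain.

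The overlap matters most for 7-day recurrence. Section 2.6 defines it in the same way as 90-day recurrence over a shorter window, so every 7-day event is also a 90-day event, and the 90-day label is what the models are trained on.

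There is also a problem of comparability. For one and the same outcome, LR and XGBoost CPRs would be reported on 2,763 patients, most of them already seen by the models, and MLP CPRs on 691 unseen patients.

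The protocol applies the opposite principle elsewhere. The section on further evaluation of the primary analysis models leaves the MLP out of testing on the non-AF cohort because that cohort helped to train it.

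**Working it through.** **The plan's split.** 0.75 × 2,763 = 2,072.25 and 0.25 × 2,763 = 690.75. Rounded, these are 2,072 and 691, and 2,072 + 691 = 2,763. The stated figures reproduce.

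**Overlap between training and secondary evaluation.**

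| CPRs from | Evaluation set | Training patients in it |
|---|---|---|
| LR, XGBoost (Table 3) | 2,763 | 2,072 / 2,763 = 75.0% |
| MLP (Table 4) | 691 | 0 / 691 = 0% |

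**Size of the optimism.** The documents give no data for this, so it was simulated on assumed inputs:
- eight binary predictors with assumed prevalences, having either no effect or weak effects (log odds ratios 0.05 to 0.30);
- 90-day recurrence at 5% and 25%, the ends of the range in Section 2.7;
- 30% of recurrences within 7 days;
- death in 35% of patients with recurrence and 15% of those without.

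A ridge logistic model was fitted to 2,072 patients. Its coefficients were turned into one, two or three points by quartile, with zero for a negative coefficient. This stands in for the SHAP tiers. The fixed points score was then scored on all 2,763 patients and on the 691 held out, in 600 datasets per setting. Mean AUCs follow (differences taken before rounding):

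| Recurrence rate, effects | 7-day recurrence: all / t / difference | Mortality: all / t / difference |
|---|---|---|
| 5%, none | 0.536 / 0.504 / +0.032 | 0.503 / 0.501 / +0.002 |
| 5%, weak | 0.576 / 0.551 / +0.026 | 0.506 / 0.504 / +0.002 |
| 25%, none | 0.514 / 0.498 / +0.015 | 0.504 / 0.499 / +0.005 |
| 25%, weak | 0.557 / 0.550 / +0.007 | 0.516 / 0.513 / +0.004 |

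For 7-day recurrence the excess is thus about +0.01 to +0.03. A second simulation on other assumed inputs agrees: 0.617 against 0.592 (+0.025) at 5% recurrence and 0.609 against 0.598 (+0.011) at 10%.

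For mortality the excess is small because the death label is never used in training. Optimism reaches it only through its association with recurrence. HT and functional decline are in the same position, but were not simulated.

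**Precision on t.** Expected 7-day events in t at 5% recurrence are 691 × 0.05 × 0.30 = 10.4, against 2,763 × 0.05 × 0.30 = 41.4 in the whole dataset. In the simulations, the standard deviation of the 7-day AUC of the points score was 0.041 to 0.096 on t and 0.020 to 0.044 on the whole dataset. That is about twofold, as expected from √(2,763/691) = 2.0.

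**The case against.** The best defence is that little of consequence is at risk. The primary outcome is evaluated on t, and the net-benefit ranking with its choice of three CPRs is described there too. The documents do not explicitly plan to rank LR/XGBoost against MLP CPRs on secondary outcomes. Section 2.12.4 already evaluates CHA2DS2-VASc on the whole AF dataset, so Table 3 can compare scores in the same patients. Moving to t also adds more random error for 7-day recurrence than the bias it removes.

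Most of this stands, and it limits the severity. It does not remove the point. Sharing patients does not cancel optimism that only one of the two scores carries. Random error is shown by a wider interval, whereas the optimism would go unreported. Readers will also set results for the same outcomes from Tables 3 and 4 next to each other, planned ranking or not.

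Three stronger readings are tempting, and the documents do not support them:
- *All secondary results are materially inflated.* Only 7-day recurrence shares its events with the training outcome. Labels for HT, functional decline and mortality never enter training.
- *The bias is as large as the improvement sought.* Table 1 expects CHA2DS2-VASc below 0.6 at worst and below 0.7 at best, and Table 3 hopes for fair to good discrimination (bands 0.71–0.80 and 0.81–0.90). For the primary outcome that gain is well above 0.03 over most of those ranges, and no margin is set for secondary outcomes.
- *XGBoost-derived CPRs must be more optimistic.* This was not simulated. The CPR Development section reduces each model to eight features worth zero to three points, with at most three interaction pairs and three extra points. This restricts what any of the models can carry over.

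**Conclusion.** The point holds as an internal contradiction with a modest bias in favour of the secondary hypothesis. Table 3 conflicts with Table 4 and with the CPR Evaluation section. Three quarters of its secondary evaluation set is training data.

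The optimism is direct for 7-day recurrence, roughly +0.01 to +0.03 in AUC for points-based scores over the 0.05–0.25 recurrence range. It is about +0.002 to +0.005 for mortality, and is judged, not shown, to be small for HT and functional decline. These sizes rest on assumed predictor prevalences, weak or null effects, a 30% share of early recurrences, and points taken from LR coefficients without interaction rules. The overlap and the mismatch of patient sets rest on the documents alone.

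This should be fixed. A reader might infer that the primary evaluation is compromised as well; it is not, because it uses t.

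**What to change.** In Table 3, in both the sampling plan and the analysis plan, make t the evaluation set for every secondary outcome, for all CPRs and for CHA2DS2-VASc. That agrees with Table 4 and the CPR Evaluation section. If whole-dataset results are also shown, label them as apparent performance and do not use them to test the hypothesis that the new CPRs do better than CHA2DS2-VASc.

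This is a wording change to one table. Its price is precision: intervals about twice as wide, and possibly only about 10 seven-day events in t, so the text should say that 7-day results will be imprecise.

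Optimism correction over all 2,763 patients, applied to every new CPR alike, would recover precision but is not a wording change. The CPR Development section relies on inspecting a dot plot, tailoring tier boundaries and adding interaction pairs from domain knowledge. These steps would first have to be fixed as mechanical rules before they could be repeated in each fold or bootstrap sample.
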